### Intervention Period

During the 10-week intervention period, participants will continue to wear their Fitbit and complete the same weekly survey (SRBAI and a single-item assessing overall health from the EuroQol EQ-5D-5L) as during the baseline period. Additionally, participants will receive an automated multicomponent BCT intervention package consisting of 7 SMS text messages daily via REDCap (delivered using the Alerts and Notifications application) with 4 BCTs to promote a walking habit of taking an additional 250 steps per hour for the same 4 hours each day.

### BCT Intervention

#### Overview

Participants will receive 4 BCTs daily (Goal setting, Action planning, Prompts/cues, and Self-monitoring of behavior) to encourage walking 250 steps per hour for 4 consecutive hours per day. Each BCT is delivered as an individual SMS text message to the participant’s cell phone. Participants are not required to respond to the BCT text message, as REDCap is not equipped to receive and store data from SMS text message responses, and to reduce perceived participant burden. These BCTs have all been previously used in interventions to reduce sedentary behavior [40-45]. One study has shown the combination of Action planning and Self-monitoring to be especially effective in reducing sedentary behavior time [40]. These are the BCTs hypothesized to increase the probability of successful habit formation [37]. Figure 4 presents a conceptual model linking the 4 intervention components of the BCT intervention, the MoBC behavioral automaticity, and the primary outcome of habit formation.

**Figure 4. F4:**
[figure not shown]
Conceptual model linking the behavior change technique intervention, mechanism of behavior change, and primary outcome of habit formation.

Some previous research has shown that caregivers spend 12 (SD 2.8) hours being sedentary per day and receive an average of 7.6 (SD 1.2) hours of sleep per night [6,46]. Spending more than 7 hours per day in a nonsedentary position is associated with a reduced likelihood of developing metabolic syndrome [47]. Furthermore, an additional 250 steps per hour for 4 hours translates to an additional 1000 steps per day, which has been found to have beneficial effects on physical and psychological health in previous research [48-50]. We deduce that 4.4 hours of caregivers’ waking hours are nonsedentary (24-h d –12 h sedentary per d – 7.6 h of sleep per night). Successful disruption of sedentary behavior with 1000 steps per day spread across a 4-hour block (250 steps per h) would result in caregivers achieving an average of over 8 hours of nonsedentary hours per day (4.4 nonsedentary h+4 additional nonsedentary h with successful disruption). This meets the average number of hours per day (>7 h) spent in a nonsedentary position to reduce metabolic syndrome while also meaningfully increasing daily steps and in a feasible manner (eg, in short bursts that disrupt sedentary time).

Below is a definition of each BCT and the delivery timing [38]:

#### 1.1 Goal Setting (Behavior)

Goal Setting is defined as encouraging an individual to set or agree on a goal, defined in terms of the behavior to be achieved (eg, take 1000 steps today). Caregivers will set a goal of taking 250 steps each hour for 4 consecutive hours, constituting a 4-hour walking block. They will receive the Goal Setting BCT daily via SMS text message at their preferred time to receive SMS text messages to encourage them to set a goal for their next 4-hour walking block.

#### 1.4 Action Planning

Action planning is defined as a prompt for detailed planning of the performance of the behavior that includes context, frequency, duration, and intensity. Caregivers will identify a plan to facilitate hourly movement during the day. They will receive the Action Planning BCT daily via SMS text message at their preferred time to receive SMS text messages to develop a plan for taking steps during their next 4-hour walking block.

#### 7.1 Prompt or Cues

Prompt/Cues is defined as introducing or defining environmental or social stimulus with the purpose of prompting or cueing the behavior, normally occurring at the time or place of performance. Caregivers will receive the Prompts/Cues BCT 4 times daily via SMS text message, one at the start of each hour during the 4-hour walking block, to prompt walking of at least 250 steps per hour.

#### 2.3 Self-Monitoring of Behavior

Self-monitoring is defined as monitoring and recording behavior. By monitoring information concerning physical activity (ie, number of steps taken), individuals can observe their progress over time. Caregivers will receive the Self-Monitoring BCT daily via SMS text message approximately 30 minutes after the end of their 4-hour walking block.

Table 1 illustrates the BCT text message prompts participants will receive in English and Spanish. A sample personalized daily BCT schedule is presented in Figure 5.

**Table 1. T1:** Description of BCTs^a^ and SMS text messages, in English and Spanish.

BCT	Language	
	English	Spanish
1.1 Goal Setting (Behavior)	Take a moment to set a goal to walk at least 250 extra steps each hour during your next walking time between *[walking period start time]* and *[walking period end time]*.	Tómese un momento para la fijación de un objetivo para caminar al menos 250 pasos más cada hora durante su próxima caminata entre *[walking period start time]* y *[walking period end time]*.
1.4 Action Planning	Think about where, when, and for how long you will walk to take at least 250 extra steps each hour during your next walking time between *[walking period start time]* and *[walking period end time]*.	Piense en dónde, cuándo y durante cuánto tiempo caminará para dar al menos 250 pasos más cada hora durante su próxima caminata entre *[walking period start time]* y *[walking period end time]*.
2.3 Self-Monitoring of Behavior	Take a moment and reflect: did you stand up and walk at least 250 extra steps each hour between *[walking period start time]* and *[walking period end time]* today? You do NOT need to respond to this message.	Tómese un momento y reflexione: ¿se levantó y caminó al menos 250 pasos más cada hora entre *[walking period start time]* y *[walking period end time]* hoy? NO es necesario que responda a este mensaje.
7.1 Prompts/Cues	It’s time to take at least 250 extra steps this hour.	Es hora de dar al menos 250 pasos adicionales esta hora.

a BCT: behavior change technique.

Participants will have an option to fully or partially (defined as passively providing Fitbit data only for the remainder of the trial) withdraw from the research at any point by reaching out to the study team as detailed in the informed consent form. Fully withdrawn participants will receive a short survey asking for the reason they are opting to withdraw from the research, and given the opportunity to complete the end-of-study surveys that all other participants complete at the end of the intervention period.

The principal investigator ([name]) will be responsible for ensuring participant safety on a daily basis. An independent local safety monitor, who is a board-certified physician, will monitor participant safety and evaluate the progress of the study according to the trial data and safety monitoring plan approved by the funder. This trial proposes a nonsystematic collection method of reported events to determine if an adverse event has occurred, and to determine next steps, if any, for reporting. Events reported by participants that meet the definition of an adverse event will be collected in electronic format using REDCap. The local safety monitor will receive regular safety reports from the principal investigator ([name]) and trial team detailing reported adverse events and will be asked to identify any issues or concerns with the interpretation and management of adverse events to ensure new safety concerns with the conduct of this research are addressed.

Participants will be paid a US $200 ClinCard (reloadable prepaid pay card) after completing the end-of-study surveys and will be able to keep the Fitbit (valued at about US $160) as a “thank you” for their participation. Additionally, participants who are in the intervention period will be entered in a random weekly lottery where one participant is selected. If the selected participant was adherent (ie, wore their Fitbit for at least 10 h/d during 6 of 7 d during that week and answered the weekly survey from that week), they will be paid a US $150 ClinCard prize. Adherence to the intervention is not a condition for the lottery. Participants who are selected for the lottery but were not adherent and therefore did not win the prize will be told as such and be given instructions on how they can become eligible for the prize next week. All other participants will be notified of their adherence the week before, and a reminder of how they can be eligible for future lottery prizes. During the 10-week intervention period, participants may be selected and awarded the lottery prize up to 10 times. Participants who are fully withdrawn or partially withdrawn from the study will be made aware that they are no longer eligible for the end-of-study compensation, but will be able to keep the study-provided Fitbit and be paid for any lottery prizes they won before withdrawing.

### General Statistical Analytical Approach

Baseline measurements will be summarized with descriptive statistics, including mean, median, and SD for continuous variables (eg, age) and proportions for categorical variables (eg, sex). In regression models, all coefficients will be estimated with 95% CIs, and for the point estimates, 2-sided *P* values will be used. All analyses will be conducted as intent-to-treat using all available data for participants who receive the intervention. We will do multiple imputation using within-subject data during the intervention as a sensitivity analysis to handle missing data. For analyses of the primary outcome, missing step data will be assessed conservatively and will be marked as having the absence of the target behavior (eg, walking 250 steps each h during their preidentified, preferred 4-h period each day for 7 consecutive d) for that day or days.

### Primary Outcome and Analysis

The primary outcome is a binary indicator of habit formation. The goal is to identify whether a significant proportion of caregivers (≥50%) develop habitual hourly walking, thereby disrupting the time they spend sedentary. A participant will have successfully formed a habit of walking if they attain walking 250 steps each hour during their preidentified, preferred 4-hour period each day for 7 consecutive days during the 70-day intervention period (Figure 6). We used this definition of habit to reflect behavioral consistency in physical activity performance. Consistency of physical activity behavior has been found to be a strong correlate of habit in previous research [84]. To ensure that our definition of habit does not bias results, we will conduct sensitivity analyses using 10-day, 14-day, and 21-day periods in addition to the 7-day period used for our primary outcome. We will use a null hypothesis rate of 30% and will compare the achieved proportion of habit formation versus this null level, using a 1-sample binomial test with a 2-sided α at 5%. The rate of habit formation will be summarized using the observed proportion along with a 95% CI. We will also use Kaplan-Meier curves to identify estimates of the time-to-event for habit formation in the sample.

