**Objective:**

The goal of the trial is to examine whether a significant proportion of ADRD caregivers (≥50%) receiving an SMS text message–delivered BCT intervention form a habit to engage in hourly walking 4 times per day, with the broader objective of disrupting sedentary time in this population.

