
### Sample Size Calculation

A sample of 100 participants is planned for enrollment into this remote trial. Up to 20% attrition is expected following the 2-week baseline period due to failure to meet wearable device and survey adherence requirements (n=20). An additional 25% attrition is expected after the 10-week intervention period due to participants becoming lost to follow-up, withdrawing, or other (n=20). The expected attrition throughout the intervention period is estimated as such because of the burdens caregivers experience due to the nature of their unique responsibilities, not limited to time constraints and motivation, which may produce barriers to longitudinal research participation [87]. We have attempted to design this trial to minimize barriers to participation for caregivers specifically, yet have estimated attrition similar to that in other longitudinal physical activity trials with caregivers to be conservative [88,89].

The trial still will have a sufficient sample (n=60) to provide adequate power. Assuming a null habit formation rate of 30% with a sample size of n=60, a 1-sided, one-sample binomial test at 5% significance will have about 92% power to declare the BCT intervention effective if the true habit formation rate is at 50% or above. We believe the null hypothesis for habit formation is conservative, as caregivers spend 80% of their time being sedentary.

To anticipate the variability due to the proposed total sample size of 60, we calculated the power to detect a difference between 20% habit formation (in the group of participants without increased behavioral automaticity) versus 60% habit formation (in the group of participants with increased behavioral automaticity) under different scenarios. Specifically, when 30% of the participants experience an increase in behavioral automaticity, there is 86% power to detect the difference. When 50% of the participants experience increases in behavioral automaticity, the power increases to about 89%.

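### The stated goal is that at least 50% form a habit, but the only primary test is against 30%, so about 41–43% is enough for a significant result

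*Protocol article*

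**What the plan says.** In the protocol article, the Abstract (Objective) says the trial will "examine whether a significant proportion of ADRD caregivers (≥50%) receiving an SMS text message–delivered BCT intervention form a habit". Primary Outcome and Analysis repeats the threshold for the primary endpoint: "The goal is to identify whether a significant proportion of caregivers (≥50%) develop habitual hourly walking".

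Later in that section the test is given: "We will use a null hypothesis rate of 30% and will compare the achieved proportion of habit formation versus this null level", by a one-sample binomial test at a two-sided 5% level. The observed proportion and a 95% CI will also be reported, but no decision is attached to the interval.

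The Sample Size Calculation section takes a null of 30% and 60 participants, and puts the power of a one-sided 5% test at about 92%. It describes this as the chance "to declare the BCT intervention effective if the true habit formation rate is at 50% or above". Declaring the intervention effective is therefore tied to rejecting 30%. The 50% figure is the assumed truth for power.

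**The concern.** The goal attaches the word for a test result (significant) to a threshold that is never tested. A reader who sees a significant primary result beside that goal will take it that at least half of caregivers formed a habit. The test supports only a rate above 30%, and at its rejection boundary fewer than half have formed a habit.

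The Discussion (Principal Results) says success would inform Stage III effectiveness trials, so it should be clear what a positive result means.

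**Working it through.** **Inputs**
- Goal: 50% or more (Abstract, Objective; Primary Outcome and Analysis).
- Null rate 30%, two-sided 5% (Primary Outcome and Analysis); one-sided 5% in the Sample Size Calculation.
- True rate for power 50%, n = 60 (Sample Size Calculation).
- Possible analysis sizes: 100 − 20 = 80 enter the intervention; 25% of 80 = 20 are lost, leaving 60. The General Statistical Analytical Approach analyses everyone who receives the intervention and counts missing step data as absence of the behavior, which points to about 80. The power statement uses 60. Both are shown.

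**Formula.** For X ~ Binomial(n, p), P(X ≥ r | p) = Σ C(n,k) p^k (1−p)^(n−k), summed over k = r to n. The critical count is the smallest r with P(X ≥ r | 0.30) ≤ 0.05 (one-sided) or ≤ 0.025 (upper tail of the two-sided test). Confidence intervals are exact (Clopper–Pearson).

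**Step 1: reproduce the plan's power.** With n = 60 and one-sided 5%, r = 25. P(X ≥ 25 | 0.30) = 0.036 and P(X ≥ 25 | 0.50) = 0.922. The stated figure of about 92% is confirmed, and it is the power to reject 30%.

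**Step 2: smallest result that rejects 30%**

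| Rule | n = 60 | n = 80 |
|---|---|---|
| Two-sided 5% | 26/60 = 43.3%, p = 0.033, 95% CI 30.6–56.8% | 33/80 = 41.3%, p = 0.037, 95% CI 30.4–52.8% |
| One-sided 5% | 25/60 = 41.7% | 32/80 = 40.0% |

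Every combination of sample size and sidedness puts the boundary at 40–43%.

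**Step 3: result needed to show a rate above 50%.** The exact lower 95% limit exceeds 50% from 39/60 = 65.0% or 50/80 = 62.5%.

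**Step 4: how often the test is significant when the goal is not met (two-sided rule)**

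The true rates of 40% and 45% are assumptions chosen to lie below the goal.

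| True rate | Event | n = 60 | n = 80 |
|---|---|---|---|
| 40% | Significant against 30% | 0.344 | 0.452 |
| 45% | Significant against 30% | 0.650 | 0.784 |
| 45% | Significant and fewer than half form a habit: P(26 ≤ X ≤ 29) or P(33 ≤ X ≤ 39) | 0.392 | 0.568 |

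**The case against.** The strongest reply is that a 30% null powered at 50% is an ordinary single-arm design, with both values openly stated. The article says it will examine or identify whether half form a habit, not that it will show it, and the Introduction restates the goal without any 50%. Nowhere does it say that rejecting 30% proves 50% or more. The observed proportion and its CI will be published, so a result of 26/60 would be visible as 43.3%. The 39/60 and 50/80 benchmarks are also severe: at a true rate of exactly 50%, which meets the goal, a lower limit above 50% would occur only 1.4% (n=60) or 1.6% (n=80) of the time.

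Much of this is fair. The design is legitimate, the reported CI helps, and a lower limit above 50% is unlikely to have been the intended success rule. The mismatch remains. Testing 30% does not identify whether the rate reaches 50% any more than it shows it: at the two-sided boundary the 95% CI includes 50% for both sample sizes, so a significant result could leave the stated question open. Nor is this detail left to a separate analysis plan, because the goal and the test are both fully stated here and do not match.

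**Conclusion.** The concern holds. The article's goal concerns 50%, and its only primary decision rule concerns 30%. A significant result is possible from 43.3% (n=60) or 41.3% (n=80). With a true rate of 40%, it occurs with probability 0.34 or 0.45.

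The boundaries rest on an exact binomial test and on an analysis set of 60 or 80. The article is not consistent on sidedness, which is a separate matter and does not alter the conclusion. The probabilities also depend on the assumed true rates.

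The test itself is valid. What needs correcting is the conclusion it is said to support, and this should be done before results are known.

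**What to change.** In the Abstract's Objective and in Primary Outcome and Analysis, state the hypothesis as the test has it: that the proportion forming a habit exceeds 30%, with 50% named as the design alternative used for power. Add one sentence on interpretation: whether the rate is 50% or more will be described from the estimate and its 95% CI, and the rate will be called significantly above 50% only if the lower 95% limit exceeds 50%.

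This changes no test, sample size or data collection. The cost is a more modest headline claim. The article expects data collection to finish by June 2026 and analysis by Fall 2026, and the wording should be settled before then.

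The alternative, making 50% the tested threshold, is not practical at this size. The chance that the lower limit exceeds 50% would be only 0.257 (n=60) or 0.369 (n=80) at a true rate of 60%, and 0.559 or 0.724 at 65%.

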### Potential Limitations

A limitation of this trial includes possible issues with the generalizability of the study findings. Based on the demographic makeup of caregivers of people with ADRD across the United States, a majority female sample is expected [7]. A second limitation is that this trial was not designed to capture nonwalking sedentary interruptions, such as periods of standing, by nature of the research objective, and the use of Fitbit wearable devices to collect continuous data. While there is some evidence that disrupting prolonged sitting behavior with standing has positive health associations, the positive health outcomes associated with disrupting sedentary behavior with walking are much more demonstrated and understood in the literature, hence the focus of this efficacy trial [90-94]. A third limitation is that we identified behavioral consistency for hourly walking (eg, walking 250 steps per h for 4 consecutive h and for 7 days in a row) as a definition for our primary outcome of habit formation. This metric was used to allow us to use a dichotomous measure of habit formation while also capturing the time duration required to achieve formation of habit. However, multiple additional criteria could easily be used to determine the presence or absence of habitual behavior. We will also be measuring daily steps longitudinally over the full duration of the trial to address this. Additional limitations may be with SMS text message fatigue, intervention fatigue, and/or low participant engagement, all of which could subsequently lead to missing data, as caregivers are a population who already experience burden and so may have barriers to completing the trial successfully. Our trial is intentionally designed with caregivers’ unique needs in mind (eg, no in-person study visits, use of electronic survey data capture, and personalized intervention times). We also intentionally designed the trial to deliver the daily components of the BCT intervention using concise language and as behavioral “nudges” that do not require engagement (eg, a response) from the participant to reduce perceived messaging or intervention fatigue. Yet, it may still be that participation is not feasible for all caregivers. Strategies will be implemented to alleviate perceived challenges of participating in the research throughout the trial, including weeknight and weekend clinical research staff support for caregivers who may only be available outside of standard business hours, providing caregivers the option to pause participation due to unanticipated circumstances and resume at a better time, and, if the caregiver wishes to withdraw from the research, offering caregivers the option to partially withdraw by passively providing only Fitbit data (rather than fully withdraw). Additionally, we have statistical methods and sensitivity analyses to manage missing data as described in the Methods section.

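### The habit-definition sensitivity analyses only lengthen the unbroken run, so they test whether 7 days is too lenient but not whether the no-missed-day rule is too strict

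*Protocol article*

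**What the plan says.** Under Primary Outcome and Analysis, a participant has formed a habit if the step target is met in every hour of the "preferred 4-hour period each day for 7 consecutive days during the 70-day intervention period". The same section sets out the only alternative definitions, together with their purpose: "To ensure that our definition of habit does not bias results, we will conduct sensitivity analyses using 10-day, 14-day, and 21-day periods".

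Under General Statistical Analytical Approach, "missing step data will be assessed conservatively and will be marked as having the absence of the target behavior", so an unrecorded day breaks a run just as an observed short day does. A separate analysis deals with missing data: "We will do multiple imputation using within-subject data during the intervention as a sensitivity analysis to handle missing data".

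Potential Limitations concedes that "multiple additional criteria could easily be used to determine the presence or absence of habitual behavior". Its answer is that daily steps will be measured throughout the trial. It names no other habit rule.

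**The concern.** A set of sensitivity analyses meant to rule out bias from a definition should vary the features of that definition that could move the answer in either direction. The primary definition has two such features: the length of the run (7 days) and the requirement that no day in it is missed. The planned variants change only the first, and only upwards. All four definitions keep the second, so they ask for 28, 40, 56 or 84 successful hours (4 hours times 7, 10, 14 or 21 days) with no day lost.

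Take a participant who meets the target on six days of every week for ten weeks and always misses the same weekday. That participant has no habit under any of the four definitions. If such people are common, the 7-day rate understates regular walking, and nothing planned would show it. At stake is what the report may say about robustness. The primary test itself is not affected.

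**Working it through.** **Inputs from the article.** 70 intervention days; run lengths 7, 10, 14 and 21; null rate 30% and goal 50% (Primary Outcome and Analysis; Sample Size Calculation). The article gives no figure for the sensitivity rates. The only stated figure on this outcome is the power of about 92% for 30% against 50% with n=60, one-sided 5%. It reproduces: the exact binomial rule is at least 25 of 60, with type I error 0.0362 and power 0.9225.

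**Step 1, nesting (no assumptions).** A run of 21 successful days contains runs of 14, 10 and 7. Writing R_L for the proportion with a run of at least L days, R_21 ≤ R_14 ≤ R_10 ≤ R_7 in every possible data set. The rate can stay the same or fall; it cannot rise.

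**Step 2, size with one common daily success rate p.** The value of p is an assumption, with days independent. Let the state be the current run length. Each day it goes up by one with probability p and returns to 0 with probability 1−p, and L is absorbing. R_L(p) is the probability of being in state L after 70 days.

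| p | 7-day | 10-day | 14-day | 21-day | at least 6 of 7 |
|---|---|---|---|---|---|
| 0.5 | 0.230 | 0.030 | 0.002 | 0.000 | 0.794 |
| 0.6 | 0.551 | 0.143 | 0.018 | 0.0005 | 0.973 |
| 0.7 | 0.870 | 0.444 | 0.117 | 0.009 | 0.999 |

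The daily rate that yields 30% is 0.526, 0.660, 0.764 and 0.858 for the four run lengths. A 30% benchmark therefore stands for a different level of walking under each definition.

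**Step 3, participants who differ.** A common p exaggerates the contrasts. Let p follow a beta distribution with mean m and concentration c, average R_L(p) over it, and solve for m so that the 7-day rate equals the design value.

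| 7-day rate | c | 10-day | 14-day | 21-day | at least 6 of 7 |
|---|---|---|---|---|---|
| 50% | 1 | 41% | 34% | 26% | 60% |
| 50% | 2 | 37% | 26% | 17% | 66% |
| 50% | 4 | 32% | 18% | 8% | 72% |
| 50% | 10 | 24% | 10% | 2% | 81% |
| 30% | 1 | 23% | 17% | 12% | 40% |
| 30% | 2 | 19% | 12% | 7% | 45% |
| 30% | 4 | 16% | 8% | 3% | 52% |
| 30% | 10 | 11% | 3% | 1% | 63% |

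Allowing one miss at the same 7-day length adds 10 to 31 points when the 7-day rate is 50% (60−50 to 81−50), and 10 to 33 points when it is 30% (40−30 to 63−30). From a 7-day rate equal to the null, the 6-of-7 rate lies above 30% at every spread, and above the 50% goal at c=4 and c=10.

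**Step 4, which relaxed rule isolates the feature.** With the 7-day rate at 50%, at least 12 of 14 days gives about 44-48% and at least 18 of 21 days about 26-42%. Both combine a longer window with tolerance, and the two effects pull against each other. At least 6 of 7 days keeps the length fixed and changes only the tolerance.

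**The case against.** The longer runs do serve a purpose. In a single-arm trial, an obvious threat is that some 7-day run within 70 days is too easy to achieve: at p=0.5, 23% would reach one by chance, against 3% for a 10-day run. The planned variants address that. A reader might infer that they say nothing about bias in the definition; the article does not support that, because they cover one direction of it.

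A reader might also infer that the variants will almost certainly make the trial look non-robust. That depends on how much participants differ and on whether the longer runs are tested against 30%, which the article does not say. With wide spread (c=1) the 10-day rate is still 41%.

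It is tempting, too, to call 6 of 7 days the trial's own walking standard. It is not. The phrase "wore their Fitbit for at least 10 h/d during 6 of 7 d during that week" (Ethical Considerations) is a device-wear condition for the lottery, and the same section says that following the intervention is not required for it. A 6-of-7 walking rule is an analyst's choice, justified because it isolates one feature.

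The no-miss rule is deliberate, chosen to reflect consistency, and the definition is listed as a limitation. Multiple imputation can restore some runs broken by missing days. Finally, the article does not repeat the word consecutive for the longer periods, and the unseen analysis plan may define them more fully. All of this stands, but it supplies no relaxed rule: imputation leaves observed short days as failures, and measuring daily steps is not a definition. The article itself fixes both the variants and the purpose they are to serve, so the mismatch is not a detail left for later.

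**Conclusion.** The concern holds as a matter of one-sided coverage. On the natural reading of unbroken runs, the three variants can never raise the rate, so they cannot support the assurance that the definition does not bias the result. They can show whether 7 days is too lenient; they cannot show whether one missed day is too strict a disqualifier.

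The nesting needs no assumptions. The sizes in Step 3 assume independent days within a participant and a beta spread between participants; neither is given in the article, and runs of good and bad weeks would change the figures. Within that range the untested feature moves the rate by roughly 10 to 33 points, which is enough to matter against a 30% null and a 50% goal. The primary test, null rate and sample size are unaffected. This should be put right before analysis, but it does not threaten the trial.

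**What to change.** 1. Add one relaxed definition of the same length: target met on at least 6 of 7 consecutive days. At least 12 of 14 days is optional as a longer tolerant window.
2. Add the proportion of intervention days on target as a continuous measure.
3. Report the 10-, 14- and 21-day unbroken runs as descriptive rates with 95% CIs, and say that they probe leniency only. The 30% null was set for the 7-day rule, so do not carry it over to any variant, strict or relaxed.
4. Replace the statement that the analyses ensure freedom from bias with one saying that they describe how the rate changes with run length and with tolerance of a missed day.

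The cost is two or three more sensitivity estimates, derived from step data already being collected, with no added participant burden. They should be specified before the analysis planned for Fall 2026. The primary analysis does not change.
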